### *Participant compensation*

Subjects will be offered compensation for their time and any inconvenience caused by their participation. They will receive 5 CHF vouchers as they complete the baseline, the first follow-up and the second follow-up steps. They can choose to purchase music online or donate the vouchers to a favorite charity.

**2.3.4 Data and data collection**

### *Instrument to evaluate the outcome*

The assessment at baseline and at each of the two follow-up points will consist of a self-completed electronic questionnaire that will include validated instruments and additional questions. Alcohol consumption will be collected via quantity/frequency questions (“In a given day that you use alcohol, how many drinks are you drinking?” / “On how many days in a regular week are you drinking alcohol?”). Additionally, participants will complete the Alcohol Use Disorders Identification Test (AUDIT)(21, 22). The AUDIT is a 10-question measure that has been extensively studied and validated, and has been used successfully in other electronic brief interventions (14, 27). Participants will also report their heaviest alcohol use on a single occasion over the past 3 months. Alcohol-related consequences will be assessed using 12 questions adapted from a questionnaire developed by Wechsler et al., 1994 (37). Subjects will be asked two supplemental questions about the impact of alcohol on their physical and mental health (“Over the past year, do you think your alcohol drinking had a negative impact on your physical health” / “your mental health?”).

Identical measures will be used at baseline and at each of the two follow-ups. When necessary, questions that are time-referenced (e.g. “over the past x months…”) will be adapted to accommodate each of the follow-up points (i.e. “over the past month…”, “over the past 5 months…”, or “since the last time we asked you about your drinking...”).

Statistics on website use (e.g. number of topics accessed, time spent on the feedback, etc.) will be collected for each participant.

***Sample size calculation***

We used data from a previous study conducted in the same setting and with the same population to approximate the alcohol consumption data (34), data from a recent publication in the field to approximate the response and attrition rates (28), and data from the [www.alcooquizz.ch](http://www.alcooquizz.ch) website to evaluate the proportion of individuals with unhealthy alcohol use.

Statistical considerations

The sample size calculations are based on the primary outcome variable comparing the mean number of drinks per week in the intervention group with the mean number of drinks per week in the control group. We have two different hypotheses based on whether or not participants have unhealthy alcohol use. In both cases, we will compare the mean number of drinks per week of the intervention group to those of the control group.

*Participants with unhealthy alcohol use:*

Null hypothesis: the mean number of drinks per week is the same between groups (alternative hypothesis: μ1≠μ2), mean number of drinks per week in the intervention group (SD): 15.0 (13.0), and in the control group (SD): 12.0 (13.0). Delta=3.0, with σ=13.0 in both groups. Considering 80% power to detect a 3 drinks per week difference in the mean number of drinks per week at follow-up (alpha level 0.05), we need 295 participants in each group to reject the null hypothesis.

*Participants without unhealthy alcohol use:*

Null hypothesis: the mean number of drinks per week is the same between groups (alternative hypothesis: μ1≠μ2), mean number of drinks per week in the intervention group (SD): 2.5 (4.7), and in the control group (SD): 4.0 (4.7). Delta=1.5, with σ=4.7 in both groups. Considering 80% power to detect a 1.5 drinks per week difference in the mean number of drinks per week at follow-up (alpha level 0.05), we need 155 participants in each group to reject the null hypothesis.

Based on previous studies in the same setting and on [www.alcooquizz.ch](http://www.alcooquizz.ch) data, we expect a >50% prevalence of unhealthy alcohol use among E-SBI participants (3). In each of the intervention and the control groups, we will need 295 participants with unhealthy alcohol use and 155 participants without unhealthy alcohol use (i.e. 450 participants per group).

According to results from other electronic interventions, we might expect the loss to follow-up to be 30% at 6 months. Using e-mail and telephone reminders and other C-SURF procedures, such as invitations and tracking teams, we should be able to reduce the loss to follow-up to 20% or less. The sample size (n=450 per group) was adjusted accordingly (n=600 per group). Previous studies in the field suggest that we should obtain a 50% refuse/decline rate among those accessing the website. In order to randomize 1200 participants into 600 participants per group, we will need to invite 2400 potential participants. Therefore, by inviting all C-SURF French-speaking participants (n=3500), we should be able to recruit an adequate number of subjects for the proposed project (Figure 1).

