**1. Summary of the research plan**

**Background:** Unhealthy alcohol use is a leading cause of morbidity and mortality among young adults. Face-to-face brief interventions targeting alcohol use are considered effective in primary care settings, but young individuals tend to have limited contacts with the health care system and are therefore unlikely to receive any intervention. As a result, electronic brief interventions have been developed that can reach a broad population at relatively low cost and potentially impact the public health system. Electronic screening and brief interventions (E-SBI) targeting alcohol use are effective among college students, but more evidence is needed in order to evaluate E-SBI designed for young individuals in other settings. There is also a lack of knowledge about the primary prevention effects of these interventions on, for example, moderate drinkers.

**Specific aims:** We will adapt our website [www.alcooquizz.ch](http://www.alcooquizz.ch) to evaluate the efficacy of a proactive E-SBI providing personalized feedback and information on alcohol use and its consequences among young men in the general population, and to help determine how young men will use E-SBI to obtain information on alcohol use and its consequences.

**Working hypothesis:** It is hypothesized that E-SBI will decrease later alcohol use and related consequences among individuals with unhealthy alcohol use (defined as >=21 drinks/week or at least one episode/month with 6 or more drinks on the same occasion) and will prevent the increase of alcohol use among individuals without unhealthy alcohol use, compared to the control condition. Among individuals with unhealthy alcohol use, the study aims to detect a 3 drinks difference in the mean number of drinks/week at follow-up (1.5 drinks difference among individuals without unhealthy alcohol use) between subjects in the intervention and control groups (alpha level 0.05, 80% power).

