***Electronic screening and brief intervention***

As a result, the use of internet and computer-based electronic interventions has been increasing over the past years. It allows the delivery of brief interventions 24 hours a day at the subjects’ convenience in the comfort of their own homes, and gives access to a much broader population than that found in primary care facilities. It is also a relatively inexpensive procedure (14). Most of the known electronic screening and brief interventions (E-SBI) are based on social norms interventions, and contain personalized feedback. According to social norms theory, our perceptions and beliefs of what is “normal” behavior among others will influence our own behavior (15-18). Believing that others drink heavily will impact one’s own drinking. The difference between one’s actual behavior and what one thinks is true of others is considered a “misperception”, and research among college students has established that a high level of misperception is associated with higher levels of alcohol use, and that perceived norms are a strong predictor of alcohol use (18-20). Electronic and face-to-face SBI aiming for the reduction of this misperception (by means of normative feedback) are considered effective for college students (11). In addition to normative feedback, available E-SBIs offer a broad range of personalized feedback and information, such as feedback on blood alcohol concentration (BAC), the monetary impact of alcohol consumption, recommendations regarding drinking, suggestions on how to cut down or on how to avoid risky situations, etc.

[www.alcooquizz.ch](http://Www.alcooquizz.ch), an E-SBI website in French developed in Lausanne, Switzerland, was launched July 15 2010. From July 15 to August 15 2010, 13,427 individuals accessed the website, of whom 11,472 (85%) fully completed the assessment and received personalized feedback. The mean age (SD) was 36.6 (13.0), 68.6% were men, and 57.7% had an Alcohol Use Disorders Identification Test >8 (21, 22), indicating probable problem drinking. Men reported a mean of 15.3 drinks per week and women a mean of 9.0 drinks per week. E-SBI appears to be feasible in Switzerland, since more than half of those accessing the website had AUDIT scores >8.

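### The stated 80% power in both drinking strata does not follow from the plan's inputs: only the total is sized, and it suits both strata only near 65.6% unhealthy use, against a stated floor of 50%

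*Protocol*

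**What the plan says.** The Sample size calculation treats participants with and without unhealthy alcohol use as two hypotheses, each tested two-sided ("alternative hypothesis: μ1≠μ2").

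- With unhealthy use, the inputs are "Delta=3.0, with σ=13.0 in both groups" and the aim is "Considering 80% power to detect a 3 drinks per week difference in the mean number of drinks per week at follow-up (alpha level 0.05"). This gives 295 per group.
- Without unhealthy use, the difference is 1.5 drinks per week with SD 4.7, at the same alpha and power. This gives 155 per group.

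The two are then added. In each group "we will need 295 participants with unhealthy alcohol use and 155 participants without unhealthy alcohol use (i.e. 450 participants per group"). The only statement about how participants will divide between the strata is "we expect a >50% prevalence of unhealthy alcohol use among E-SBI participants (3"). It is attributed to earlier studies in the same setting and to the website data.

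The next paragraph raises 450 to 600 per group. It mentions 30% loss seen with other electronic interventions and a target of 20% or less. Figure 1 shows 1200 randomized and 900 assessed at 6 months. Randomization is stratified by drinking status, and the Efficacy analysis section keeps the strata apart in all analyses. The Summary repeats the aim without conditions: in the unhealthy-use stratum "the study aims to detect a 3 drinks difference in the mean number of drinks/week at follow-up", with 80% power.

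**The concern.** The strata are tested separately, so the number in each stratum sets its power, and the total does not. Adding 295 and 155 and recruiting to the sum works only if participants happen to divide in that ratio. Stratified randomization balances the two groups within each stratum, but it does not determine how many people the stratum holds. The eligibility criteria and the Recruitment section contain no quota or minimum per stratum.

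The protocol never states the split that its total requires, and its one expectation is a floor well below that split. If the mix is off, one stratum is underpowered while the other has power to spare. A null result in the short stratum could then be read as lack of efficacy in a comparison that the protocol describes as having 80% power.

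**Working it through.** **Inputs.** Two-sided alpha 0.05, power 80%, equal allocation; difference 3.0 with SD 13.0, and difference 1.5 with SD 4.7 (Sample size calculation). 600 randomized per group (same section, and Figure 1). The Summary also gives a total of 1080, which disagrees with its own 600 per group; I use 1200 in total. I assume the same loss in both strata.

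**1. Reproduce the plan's figures.** n per group = 2 × (1.960 + 0.842)² × (SD/difference)².

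- With unhealthy use: 2 × 7.849 × (13/3)² = 294.8, so 295.
- Without unhealthy use: 2 × 7.849 × (4.7/1.5)² = 154.1, so 155.

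Both agree with the protocol, and 295 + 155 = 450.

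**2. Loss implied by 600.** 450/600 = 0.75, which is 25% loss and matches the 900 completers in Figure 1. A 20% loss would need 450/0.80 = 563 per group, and a 30% loss 450/0.70 = 643.

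**3. Prevalence at which both strata reach target.** With C completers per group, the unhealthy-use stratum needs a prevalence of at least 295/C, and the other stratum needs it to be at most 1 − 155/C.

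| Loss | C per group | At least | At most | Both reached |
|---|---|---|---|---|
| 20% | 480 | 61.5% | 67.7% | 61.5% to 67.7% |
| 25% | 450 | 65.6% | 65.6% | only at 65.6% |
| 30% | 420 | 70.2% | 63.1% | never |

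**4. Power by stratum with 450 completers per group** (two-sample t-test, noncentral t).

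| Prevalence | n with | Power with | n without | Power without |
|---|---|---|---|---|
| 50% | 225 | 68.5% | 225 | 92.2% |
| 57.7% | 260 | 74.7% | 190 | 87.3% |
| 65.6% | 295 | 79.9% | 155 | 80.0% |
| 70% | 315 | 82.4% | 135 | 74.3% |

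The normal approximation gives values within 0.4 percentage points of these. With 20% loss, power in the unhealthy-use stratum is 71.3% at 50% prevalence (n = 240) and 77.4% at 57.7% (n = 277). With 30% loss and 50% prevalence it is 65.5% (n = 210).

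**5. Basis for the prevalence.** The protocol says the website data were used to evaluate the proportion with unhealthy use. The only website figure of that kind is "57.7% had an Alcohol Use Disorders Identification Test >8", in visitors with mean age 36.6, of whom 68.6% were men. The trial's definition is at least 21 drinks per week or at least one episode per month of 6 or more drinks, in 20-year-old men. So 57.7% is used above only as an illustration.

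**The case against.** **Prevalence may be high enough.** A reader might infer that actual power in the unhealthy-use stratum is 69% to 75%. The documents do not support that. The expectation is a lower bound and does not exclude 65.6% or more. It also rests partly on earlier same-setting studies whose rate is not reported. The 75% end uses an AUDIT rate that is neither the trial's definition nor its population. This objection stands in full: the powers above are conditional.

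**One stratum need not fall short.** It is also tempting to say that one stratum must miss its target unless prevalence is exactly 65.6%. That is true at 25% loss. At the 20% the protocol aims for, anything from 61.5% to 67.7% suffices.

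**Nothing is miscalculated.** Correct: 295, 155 and 450 all reproduce. The gap lies in the unstated assumption about the mix.

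**The unhealthy-use comparison is not the main one.** Also correct. The protocol does not rank the two hypotheses, and either stratum can be the one that falls short.

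**All 3500 will be invited.** At the protocol's 50% rate this could give 1750 participants, or 875 per group. At 50% prevalence and 25% loss that is 328 per group with unhealthy use and about 84% power. But the stated design randomizes 1200, and nothing says enrolment continues beyond that. The margin shows that a remedy is feasible; it does not make the 80% statement follow.

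**Baseline adjustment will recover power.** ANCOVA is planned, and baseline consumption is among the possible covariates. With correlation r between baseline and follow-up, the SD becomes 13 × √(1 − r²). At 225 per group, power is about 73% for r = 0.3, 81% for r = 0.5 and 93% for r = 0.7. The documents give no correlation, so these values are assumptions and cannot carry the claim.

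**Enrolment is already monitored.** The Schedule provides for daily and weekly checks, but does not say they are made by stratum.

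**Conclusion.** The concern holds as a conditional one. The protocol claims 80% power in two separately tested strata but sizes only their sum, and the sum meets both requirements only within a narrow prevalence range that the protocol neither states nor secures. The shortfall is about 11 percentage points of power in the unhealthy-use stratum at the stated floor (25% loss), while the other stratum is well above target. It moves to the stratum without unhealthy use once prevalence exceeds 65.6%. At 30% loss, which the protocol cites from other studies, no mix is sufficient.

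These figures assume the protocol's differences and SDs, the unadjusted comparison used in its own calculation, 600 randomized per group and equal loss in both strata. They do not show that the trial is underpowered. Its true power cannot be determined from the document, because prevalence under the trial's definition is not given.

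**What to change.** - In the Summary and the Sample size calculation, including its paragraph on loss to follow-up, replace the unconditional 80% with a table of power by stratum. Cover a range of prevalence, for example 50% to 75%, and losses of 20%, 25% and 30%.
- State that 600 per group gives 80% in both strata only near 65.6% unhealthy use at 25% loss, or 61.5% to 67.7% at 20% loss.
- Give an expected prevalence under the trial's own definition, taken from the earlier same-setting data, and stop relying on the website AUDIT rate.
- Monitor enrolment and completers by stratum against 295 and 155 per group, instead of the total against 450.
- Show any gain from baseline adjustment only as a sensitivity over an assumed range of correlations.

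The cost is revised wording, one table and a stratum split in checks that are already planned. These changes do not by themselves require more participants. The downside is that the stated power becomes less favourable.

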***Diagnostic statistics***

Descriptive statistics, such as mean, median, standard deviation, range, minimum, maximum, frequencies and plots, etc., will be computed for baseline, primary and secondary outcome variables. Except for the presence or absence of unhealthy alcohol use, primary and secondary outcomes are continuous. Randomization results, data distribution, variability and outliers on primary and secondary outcome data will all be checked. The diagnostic results will be used to describe the study population and to base statistical modeling and use of non-parametric tests. All exploratory analyses will be reported as such in publications.

***Efficacy analysis***

All analyses will be conducted separately for participants with and without unhealthy alcohol use in order to assess two specific hypotheses (i.e. decrease in subsequent alcohol use and related consequences among individuals with unhealthy alcohol use and no increase among individuals without unhealthy alcohol use). Efficacy analyses will be based on data collected at the E-SBI baseline, 1 month follow-up and 6 months follow-up.

*Primary efficacy analysis*

An intention-to-treat analysis will be used. In our primary analysis we will be testing the null hypothesis of no difference between mean number of drinks per week and number of RSOD episodes per month in the E-SBI and the control groups (μ1=μ2). For normally-distributed continuous data, t-tests for 2 independent samples will be calculated for the overall crude analysis. For data that are not normally-distributed, non-parametric Wilcoxon rank sum tests will be used. Then we will utilize an analysis of covariance model (ANCOVA) to control for covariates, which may include demographics, alcohol consumption, number of RSOD episodes per month and alcohol-related problems, all at baseline. Models of more complexity will take into account multiple observations, such as Generalized Estimating Equations (GEE), regressions or similar models.

*Secondary efficacy analysis*

Secondary continuous outcomes will be analyzed in the same manner as the primary outcomes.

*Additional analyses*

In addition to efficacy analyses, we will conduct usage analyses on specific website pages accessed by participants, including details of the time spent within each of the sections. These statistics will help us determine what information participants found most interesting, and assist us in further developing the electronic interventions.

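### The analysis is labelled intention-to-treat, but its lead tests by default use only men with observed follow-up, with 20-30% loss expected; dropout related to drinking differently by arm could bias them

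*Protocol*

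**What the plan says.** The primary efficacy analysis (protocol, Efficacy analysis) opens with "An intention-to-treat analysis will be used" and then sets an order of methods:

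- Crude comparison: "t-tests for 2 independent samples will be calculated for the overall crude analysis". Its alternative is: "For data that are not normally-distributed, non-parametric Wilcoxon rank sum tests will be used".
- Adjusted comparison: "Then we will utilize an analysis of covariance model (ANCOVA) to control for covariates, which may include demographics, alcohol consumption". The list goes on to heavy-drinking episodes and alcohol-related problems, and every covariate is a baseline value.
- Last: "Models of more complexity will take into account multiple observations, such as Generalized Estimating Equations (GEE), regressions or similar models". GEE is one example in an open list. Weighting is not mentioned.

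The same section says that efficacy analyses draw on baseline, 1-month and 6-month data. It does not say how men without a follow-up answer enter the intention-to-treat analysis.

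On loss, the Sample size calculation says "we might expect the loss to follow-up to be 30% at 6 months", and then, counting on reminders and cohort tracking, "we should be able to reduce the loss to follow-up to 20% or less". Figure 1 plans 1200 randomised, 960 at 1 month and 900 at 6 months.

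**The concern.** A t-test, a rank sum test and an ANCOVA each need an outcome value for every man analysed. With nothing further specified, they drop the men who did not answer, and the intention-to-treat label would then cover an analysis of about three quarters of those randomised.

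This matters only if the reason for not answering is tied to drinking, and tied differently in the two arms. The design gives a plausible route. Intervention men receive normative and risk feedback, and those with unhealthy use are encouraged to change. Controls receive no feedback. Follow-up means logging on to the study website. A man who was advised to change and has not done so may have a reason to stay away that a control lacks. If so, heavier drinkers leave the intervention arm selectively, and the intervention looks better than it is.

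The 1-month answers could partly reveal such a pattern. They play no part in the crude test or the baseline-covariate ANCOVA, and enter only through the unspecified more complex models.

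**Working it through.** **1. The plan's own figures.** With n per group = 2(1.96 + 0.84)² × (SD/delta)²:

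- Unhealthy use, delta 3.0, SD 13.0: 295.
- No unhealthy use, delta 1.5, SD 4.7: 155.
- Total 450 per group. 450/(1 - 0.25) = 600, which matches the 25% loss in Figure 1 (900/1200 = 0.75). Loss of 20% would give 563, and 30% would give 643.

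These figures reproduce. Power counts only men with follow-up. That is normal for sizing and does not by itself show that only completers will be analysed.

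**2. Assumed mechanism (not in the documents).** The true effect is zero and SD is 13. The correlation rho is the same between all three visits, 0.5 to 0.7. Loss is 25% in each arm. In controls loss is unrelated to drinking. In the intervention arm the odds of loss multiply by OR (1.5 to 3) per SD of 1-month drinking.

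Let m be the mean standardised 1-month drinking of intervention-arm completers. Integrating over a normal distribution gives m = -0.098 (OR 1.5), -0.160 (OR 2) and -0.228 (OR 3).

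- Crude bias = 13 × rho × m
- Baseline-adjusted ANCOVA bias ≈ 13 × rho × (1 - rho) × m

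| rho | OR | Crude | ANCOVA |
|---|---|---|---|
| 0.5 | 1.5 | -0.64 | -0.32 |
| 0.5 | 3 | -1.48 | -0.74 |
| 0.6 | 2 | -1.24 | -0.50 |
| 0.7 | 1.5 | -0.90 | -0.27 |
| 0.7 | 3 | -2.07 | -0.62 |

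The crude bias is therefore about -0.6 to -2 drinks/week and the ANCOVA bias about -0.3 to -0.75. The middle case is 1.24/3 = 41% of the target difference for the crude test and 0.50/3 = 17% for ANCOVA. Simulation agrees (-1.24 and -0.51). With the same mechanism in both arms, both biases are about 0.

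**3. False positives, middle case, 295 per arm.**

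- Crude: SE = 13 × √(2/295) = 1.07; 1.24/1.07 = 1.16; rejection rate about 21% instead of 5%.
- ANCOVA: residual SD = 13 × √(1 - 0.6²) = 10.4; SE = 0.86; 0.50/0.86 = 0.58; about 9%.

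**4. A second simulation with a true effect of -3.0** (rho 0.6, loss about 25% against 22%, dropout linked to drinking in the intervention arm only, 1-month values known for everyone):

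| Dropout driven by | Crude | ANCOVA | GEE, unweighted, independence, baseline-adjusted | Likelihood-type, using 1-month data |
|---|---|---|---|---|
| Baseline drinking | -4.43 | -3.03 | -3.02 | -3.03 |
| 1-month drinking | -4.40 | -3.58 | -3.57 | -3.02 |
| Unseen 6-month drinking | -5.38 | -4.53 | -4.52 | -4.35 |

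Baseline adjustment is enough when dropout follows baseline drinking. It is only partly enough when dropout follows 1-month drinking, and GEE of this form adds nothing. No listed method is enough when dropout follows the unseen value.

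**5. What the fix can recover.** The near-exact result in the second row needs 1-month data from everyone. Figure 1 plans 240 men lost at 1 month and 300 at 6 months. If those lost at 1 month stay lost, 240/300 = 80% of the men missing at 6 months have no 1-month value. Simulating that pattern under the mechanism in step 2, an analysis by arm using all available baseline and 1-month data leaves about -0.4 in the middle case and about -0.2 to -0.6 over the range.

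**The case against.** Handling of missing outcomes is commonly left to a statistical analysis plan, which may exist. The protocol does not say that only completers are analysed, and it does not exclude imputation. It allows adjustment for baseline drinking, plans models for repeated observations, and supports follow-up with e-mail and telephone reminders and vouchers. No part of the protocol indicates that non-improvers in the intervention arm will stop answering.

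Much of this stands. A missing imputation paragraph would not be a finding. This point rests on what the protocol does fix: the label, a lead test that is unadjusted, and an ANCOVA limited to optional baseline covariates.

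Three stronger readings are tempting and unsupported:

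- A reader might infer that unweighted GEE is the only repeated-measures model. It is an example in an open list that a mixed model would also fit, and weighting is simply not mentioned.
- A reader might infer that differential dropout would bias the result. Unequal loss alone does not. Dropout must relate to the outcome, and do so differently by arm.
- A reader might infer that using the 1-month data removes the bias. On the protocol's own expected loss it does not.

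**Conclusion.** The point holds as a weakness in the stated methods, not as a demonstrated bias. The lead tests by default leave out the expected 20-30% without follow-up, under a label that suggests otherwise, and the crude comparison is the most exposed of the named methods. The sizes in the working depend on an assumed one-arm dropout mechanism, normal outcomes and assumed correlations. They show what could happen in the unhealthy-use stratum and do not predict what will.

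Most of the avoidable bias goes once baseline adjustment is made mandatory and primary (from -1.24 to -0.50 in the middle case). The 1-month data bring a smaller further gain, to about -0.4 under the Figure 1 loss pattern. The protocol ties no time point to these tests. Six months is used here because the sample size is adjusted for 6-month loss. The change should be made. Confidence is medium, because the mechanism cannot be checked from the document.

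**What to change.** - State how men without follow-up enter the intention-to-treat analysis.
- Within each drinking stratum, make the primary 6-month estimate a baseline-adjusted analysis of all randomised men in their allocated arm, using the 1-month and 6-month outcomes. Either a likelihood-based mixed model or multiple imputation by arm followed by the primary model would serve. Baseline drinking should be a fixed covariate, not an optional one.
- Keep the crude completer test as supportive. If GEE is retained, state how it handles dropout.
- Add one sensitivity analysis for outcome-dependent dropout, for example assuming that intervention-arm non-responders drink as controls do.
- Report loss by arm and by baseline and 1-month drinking.

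No new data are needed. The cost is modest extra analysis and wording, and the primary model then relies on a missing-at-random assumption, which the sensitivity analysis is there to probe.

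### The primary hypothesis and sample size concern means, but a normality-dependent rule will almost certainly send the crude primary comparison to a Wilcoxon test, and no analysis is named as decisive

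*Protocol*

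**What the plan says.** All references are to the Protocol.

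- **Hypothesis.** Under Efficacy analysis, the primary analysis is described as "testing the null hypothesis of no difference between mean number of drinks per week and number of RSOD episodes per month", written as μ1=μ2.
- **Sample size.** "The sample size calculations are based on the primary outcome variable comparing the mean number of drinks per week in the intervention group" and with that in the control group. The targets are 3.0 drinks per week (SD 13.0) for men with unhealthy alcohol use and 1.5 (SD 4.7) for men without it, giving 295 and 155 per group.
- **Test rule.** "For normally-distributed continuous data, t-tests for 2 independent samples will be calculated for the overall crude analysis". Next: "For data that are not normally-distributed, non-parametric Wilcoxon rank sum tests will be used".
- **What triggers the rule.** Diagnostic statistics has the outcome data checked for distribution and outliers, and adds: "The diagnostic results will be used to describe the study population and to base statistical modeling and use of non-parametric tests".
- **What follows.** "Then we will utilize an analysis of covariance model (ANCOVA) to control for covariates, which may include demographics, alcohol consumption" and other baseline items. GEE, regressions or similar models come after that for the repeated observations. All of this sits under the primary efficacy analysis, and the text does not say which step decides the result.
- **Outcome type.** "Except for the presence or absence of unhealthy alcohol use, primary and secondary outcomes are continuous".

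**The concern.** A rank sum test and a comparison of means answer different questions. The rank test asks whether a man in one arm tends to report more than a man in the other. The hypothesis and the target differences ask how far apart the averages are. For skewed, non-negative drinking data the two can disagree in either direction.

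If the stated rule leads to the rank test, the crude primary result does not test the stated hypothesis, gives no estimate of the 3.0- or 1.5-drink difference, and has a power that was never calculated. The ANCOVA then returns to means. The primary section would thus hold two results on different scales, with nothing to say which prevails if they disagree.

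**Working it through.** **1. The plan's own figures.** For a two-sided comparison of means at alpha 0.05 and 80% power, n per group = 2(1.960+0.842)²σ²/δ².
- Unhealthy use: 2 × 7.849 × 13.0²/3.0² = 294.8, so 295.
- No unhealthy use: 2 × 7.849 × 4.7²/1.5² = 154.1, so 155.

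Both stated figures are reproduced. The trial is sized for means.

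**2. Could drinks per week be normal?** Inputs are the means and SDs under Sample size calculation. The share of a normal curve below zero is Φ(−mean/SD). Any non-negative variable has skewness of at least SD/mean − mean/SD.

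| Mean (SD) | Normal share below zero | Minimum skewness |
|---|---|---|
| 15.0 (13.0) | Φ(−1.154) = 12% | −0.29 |
| 12.0 (13.0) | Φ(−0.923) = 18% | +0.16 |
| 4.0 (4.7) | Φ(−0.851) = 20% | +0.32 |
| 2.5 (4.7) | Φ(−0.532) = 30% | +1.35 |

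Positive skew is mathematically forced in three of the four arms and very likely in the fourth. The Protocol names no normality test. If one assumes Shapiro-Wilk, it rejected in all 500 simulated samples in each of three cases tried: gamma 15 (13) with n=295, gamma 4 (4.7) with n=155, and negative binomial 12 (13) with n=295.

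For risky single occasion drinking (RSOD) the documents give no mean or SD. It is a frequency of episodes, and men without unhealthy use report less than one a month at baseline by definition, so many zeros are to be expected.

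**3. How the two tests behave.** The shape (negative binomial) is an assumption; n=295 per group, two-sided 5%. The tests are two-sided, so it does not matter which arm carries which mean.

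| Arms compared, mean (SD) | t-test rejects | Wilcoxon rejects |
|---|---|---|
| 15 (13) vs 12 (13): plan's means, equal SDs | about 80% | about 98% |
| 15 (13) vs 12 (10.4): proportional reduction, 13 × 12/15 = 10.4 | about 87% | about 79% |
| 15 (13) vs 15 (10): equal means | about 5% | about 34% |
| Identical distributions | about 5% | about 5% |

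Repeat runs differ by a point or so.

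**4. Sensitivity to the assumed shape.**
- Plan's means, equal SDs; gamma, lognormal, negative binomial and gamma with 30% zeros: Wilcoxon power is 85% to 99.7% (n=295) and 88% to 100% (n=155), while the t-test stays at 79% to 80% and 79% to 82%.
- Proportional reduction; gamma, lognormal and negative binomial: Wilcoxon is 78% to 94% and 77% to 99%, against 87% to 88% and 93% to 95% for the t-test.
- Equal means of 4 with SDs of 4.7 and 3.5 (gamma, n=155): Wilcoxon rejects in 42% of trials and the t-test in 5%.

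The t-test therefore keeps the planned power under skew. The Wilcoxon figure moves with shape and with the kind of effect.

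**The case against.** The strongest reply is that the t-test or Wilcoxon step is labelled crude. An ANCOVA that compares adjusted means follows, so the plan already contains an analysis on the scale of its hypothesis. The choice of decisive model and covariates is also commonly left to a statistical analysis plan, which may exist. This reply stands in part. A reader might infer that the Wilcoxon p-value is the trial's primary result; the Protocol does not say so. But it does not say that the ANCOVA is either, and the distribution-dependent rule is one that the Protocol itself sets.

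Other stronger readings also go too far:

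- **That Wilcoxon is invalid here.** It holds about 5% when the distributions are identical. Rejection with equal means and unequal spread reflects a real difference between arms, though not the one hypothesised.
- **That it would cost most of the power.** A very large loss can be produced by assuming that the intervention caps everyone's drinking at a fixed level. Nothing in the Protocol suggests such an effect, and a cap at 22 drinks per week would cut the SD to about 7.5, against the plan's equal SDs. On the plan's own means and SDs, Wilcoxon has more power than the t-test.
- **That choosing the test from the data inflates the type I error.** No calculation here shows it. If the branch is almost certain, the rule in effect fixes Wilcoxon in advance.
- **That the outcomes must be modelled as counts.** Weekly drinks are derived from quantity and frequency questions, and the word continuous mainly sets these outcomes apart from the binary one.

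**Conclusion.** The point holds as a mismatch between the stated hypothesis and the stated test rule, together with the lack of a decisive analysis. For drinks per week, the plan's own means and SDs make normality untenable, so the crude comparison will almost certainly be a rank test. The stated 80% power does not describe that test. The gap can go either way: in the assumed negative-binomial data it runs from 18 points above the t-test (98% vs 80%) to 8 below (79% vs 87%), and to 34% against 5% when the means are equal but the spreads differ.

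The mismatch, the reproduced sample sizes and the skewness bounds rest on the Protocol alone. The rejection rates rest on assumed shapes and should be quoted only as a range. For RSOD the conclusion rests on the nature of the outcome, since no planning values are given. Because a mean-scale ANCOVA is already planned, this should be fixed but does not undermine the design.

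**What to change.** Remove the normality-dependent switch. For each primary outcome, name one baseline-adjusted analysis of means as decisive, whatever the observed shape. The ANCOVA already planned would serve, with the baseline value of the outcome as covariate and robust or bootstrap standard errors, reporting the difference in means with its 95% confidence interval. A count model is an acceptable alternative, not a requirement. Keep Wilcoxon as a sensitivity analysis, and label the crude comparison and the repeated-measures models as supportive.

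The cost is a change of wording. The sample size can stay: under the skewed shapes tried with the plan's means and SDs, an unadjusted comparison of means kept 79% to 82% power, with a type I error of 4.7% and 5.0% in gamma data. The small downside is that a rank-based p-value is no longer available as the primary result.
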